### Patient Population Size

We expect to have statistically significant data following the collection of 300 data sets (10 distinct measurements taken from 30 unique participants). This is based on statistical analysis of previous studies.

The precision of the mean and precision of the LoAs depend on the standard deviation of the differences. We use the value of 1.79 breaths per minute as the standard deviation reported in the Lee study [12] for comparison of RespiraSense and ECG and the same value for the comparison of RespiraSense with end-tidal capnography, this being regarded as more accurate than ECG. For comparison with an HCP, we use the value of 2.5 breaths per minute, also from the Lee study.

Table 3 shows the number required for different precisions of the mean difference using 95% confidence intervals. Table 4 shows the number required for different precisions of the LoA.

**Table 3 table3:** Precision of mean at 95% confidence interval.

Breaths per minute	Precision of the mean	Standard error of the mean	N
1.79	1	0.51	13
1.79	0.5	0.26	50
1.79	0.4	0.2	77
1.79	0.3	0.15	137
1.79	0.25	0.13	197^a^
1.79	0.2	0.1	308
1.79	0.1	0.05	1231
2.5	1	0.51	25
2.5	0.5	0.26	97
2.5	0.4	0.2	151
2.5	0.3	0.15	267^a^
2.5	0.25	0.13	385
2.5	0.2	0.1	601
2.5	0.1	0.05	2401

^a^Precisions to be expected if 30 participants provide 10 data points each, allowing for a 10% loss of data.

**Table 4 table4:** Precision of limits of agreement at 95% confidence interval.

Breaths per minute	Precision of LoA^a^	Standard error of LoA	N
1.79	1	0.51	37
1.79	0.5	0.26	148
1.79	0.4	0.2	231^b^
1.79	0.3	0.15	411
1.79	0.25	0.13	591
1.79	0.2	0.1	924
1.79	0.1	0.05	3693
2.5	1	0.51	73
2.5	0.6	0.31	201^b^
2.5	0.5	0.26	289
2.5	0.4	0.2	451
2.5	0.3	0.15	801
2.5	0.25	0.13	1153
2.5	0.2	0.1	1801
2.5	0.1	0.05	7203

^a^LoA: limits of agreement.

^b^Precisions to be expected if 30 participants provide 10 data points each, allowing for a 10% loss of data.

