The RespiraSense device (PMD Solutions Ltd) was developed to improve the detection of changes in the RR in order to alert staff to out-of-range values that may be clinically significant. In a 48-patient investigation, data were collected to evaluate the difference in RR measurements between the developed RespiraSense device, electrocardiogram (ECG), and direct nursing observations [12]. A clinically relevant agreement between all RR measurements by the 3 different methods was demonstrated. However, few abnormal values were recorded in this investigation, and further research is required to ensure that the device works well to accurately measure the RR at values both higher and lower than the normal range.

**Table 1 table1:** Escalation protocol for the deteriorating patient [8].

Vital sign	Score						
	3	2	1	0	1	2	3
Pulse	≤40	—	41-50	51-90	91-110	111-130	≥131 Unrecordable due to patient condition
Temperature (°C)	≤35	—	35.1-36	36.1-38	38.1-39	≥39	Unrecordable due to patient condition
BP^a^ systolic (mm Hg)	≤90	91-100	101-110	111-219	—	—	≥220 Unrecordable due to patient condition
Respiratory rate (bpm)	≤8	—	9-11	12-20	—	21-24	≥25 or Unrecordable due to patient condition
AVPU^b^	—	—	—	Alert	—	—	Voice pain unresponsive^c^
SaO_2_^d^	≤91	92-93	94-95	≥96 or Unrecordable because patient refused, equipment unavailable, other reason	—	—	Unrecordable due to patient condition
Inspired O_2_	—	—	—	Air	—	Any supplemental O_2_^e^	—

^a^BP: blood pressure.

^b^AVPU: alert, verbal, pain, unresponsive.

^c^If AVPU is V or C due to patient sedation, it will be charted as S and score 0 rather than 3.

^d^SaO_2_: oxygen saturation.

^e^Note that “any supplemental O_2_” applies to any supplemental oxygen the patient is receiving. It does not apply to patients who are on masks through which only air is being supplied (air delivery possible through tracheostomy, bilevel positive airway pressure or continuous positive airway pressure, for example).

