Each participant will be studied in the normal position (ie, sitting at 45 degrees on a couch) for 6 different metronome rates. They will then be studied in one of the three following additional positions for an additional 4 metronome rates: supine (flat on their back), left lateral decubitus (recovery) position, or sitting at 90 degrees (chair position).

Each metronome rate will be maintained for 2 minutes with 2 to 5 minutes in between for transition (or longer if required by the participant to return to normal breathing rates). A full process flow of the requirements of each participant is shown in Figure 1.

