### Statistical Analysis

The primary end point is the RR as measured by multiple methods. The primary objective of the analysis is to examine the agreement between the RespiraSense device and the other measurement methods for this end point. The mean difference between each pair of methods will be calculated with 95% confidence intervals. Variances will be tested for nonequality with an *F* test. The distributions of the differences will be examined with Bland-Altman plots. Limits of agreement (LoAs) and proportions of measurements outside the limits will be compared. If the differences between methods markedly increase with their mean, the analysis will be repeated with a log transformation of the measurements. A secondary analysis of agreement by participant position (45 degree sitting vs other positions) for each pair of methods will be performed using an analysis of variance.

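### The precision stated in Tables 3 and 4 treats repeated epochs from 30 people as independent, so the footnoted figures are optimistic under any appreciable within-participant correlation

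*Protocol article*

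**What the plan says.** Under Patient Population Size the target is "300 data sets (10 distinct measurements taken from 30 unique participants"). The planning SDs come from one earlier study: "We use the value of 1.79 breaths per minute as the standard deviation" for the comparisons with ECG and capnography, and "For comparison with an HCP, we use the value of 2.5 breaths per minute". Table 3 gives N by precision of the mean difference and Table 4 by precision of the LoA. Four rows carry the footnote "Precisions to be expected if 30 participants provide 10 data points each, allowing for a 10% loss of data":

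- mean, SD 1.79: 0.25 (N = 197)
- mean, SD 2.5: 0.3 (N = 267)
- LoA, SD 1.79: 0.4 (N = 231)
- LoA, SD 2.5: 0.6 (N = 201)

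The section mentions no correlation between measurements on the same person.

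Under Study Design, "Each participant will be studied in the normal position (ie, sitting at 45 degrees on a couch) for 6 different metronome rates". Four more rates follow in one other position, all in a single visit.

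Under Statistical Analysis, "The mean difference between each pair of methods will be calculated with 95% confidence intervals", alongside Bland-Altman plots, LoA and an analysis of variance by position. No participant term is named, and no variance formula is given.

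**The concern.** The device, nasal cannula and ECG are attached at the start of the session. One person's ten epochs therefore share body shape, sensor placement and breathing style. The difference between two methods is likely to run high in some people and low in others, which makes epochs from one person positively correlated. The independent units are then the 30 participants, and 270 data points carry less information about the bias and the LoA than 270 unrelated differences would.

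The tables are the only quantitative support for the sample size. If their footnoted rows promise more than the design can give, readers are misled about how tightly 30 people can pin down agreement.

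**Working it through.** **Inputs from the protocol article.** 30 participants, 10 epochs each, 10% loss (270 points); SD of differences 1.79 and 2.5; 95% confidence (z = 1.96).

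**Assumed.** The ICC, shown from 0.05 to 0.3. The 10% loss is taken as spread evenly, so m = 9 usable epochs for each of J = 30 people.

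**Step 1: reproduce the tables.** For the mean, N = (1.96 × SD / d)², rounded up. For the LoA, N = 3 × (1.96 × SD / d)², rounded up. The footnoted rows give:

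- (1.96 × 1.79 / 0.25)² = 196.9, so 197
- (1.96 × 2.5 / 0.3)² = 266.8, so 267
- 3 × (1.96 × 1.79 / 0.4)² = 230.8, so 231
- 3 × (1.96 × 2.5 / 0.6)² = 200.1, so 201

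All 14 rows of Table 3 and all 15 of Table 4 reproduce exactly. Both formulas require independent differences. With 270 independent points the half-widths would be 0.214 and 0.298 for the mean, and 0.370 and 0.516 for the LoA, so all four footnoted rows would be met.

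**Step 2: mean difference with clustering.** The design effect is 1 + (m − 1) × ICC = 1 + 8 × ICC, and the effective n is 270 divided by it. The half-width is 1.96 × SD / √(effective n). At ICC 0.2 the design effect is 2.6 and the effective n is 104; the half-width is 0.34 for SD 1.79 and 0.48 for SD 2.5.

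**Step 3: LoA with clustering.** Split SD² into a between-participant part (ICC × SD²) and a within-participant part (the rest). Then:

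- MSW = within part; MSB = within part + 9 × between part
- Var(mean) = MSB / 270
- Var(total variance) = 2·MSB² / (81 × 29) + (8/9)² × 2·MSW² / (30 × 8)
- Var(total SD) = Var(total variance) / (4 × SD²)
- half-width = 1.96 × √[Var(mean) + 1.96² × Var(total SD)]

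Example, SD 1.79 and ICC 0.2: MSW = 2.563, MSB = 8.331, Var(mean) = 0.0309, Var(total variance) = 0.1024, Var(total SD) = 0.0080. The half-width is 1.96 × √(0.0309 + 0.0307) = 0.49. At ICC 0 this method gives 0.365 and 0.510, slightly below the 0.370 and 0.516 of Step 1, so it does not exaggerate the shortfall.

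| Assumed ICC | Effective n (mean) | Mean, SD 1.79 (stated 0.25) | Mean, SD 2.5 (stated 0.3) | LoA, SD 1.79 (stated 0.4) | LoA, SD 2.5 (stated 0.6) |
|---|---|---|---|---|---|
| 0.05 | 193 | 0.25 | 0.35 | 0.39 | 0.55 |
| 0.1 | 150 | 0.29 | 0.40 | 0.42 | 0.59 |
| 0.2 | 104 | 0.34 | 0.48 | 0.49 | 0.68 |
| 0.3 | 79 | 0.39 | 0.55 | 0.56 | 0.78 |

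The 0.25 at ICC 0.05 is 0.253 before rounding, just past the stated figure.

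**Step 4: where each row is lost.** For the mean, solve 270 / (1 + 8 × ICC) = N. This gives (270/267 − 1)/8 = 0.0014 for the 0.3 row and (270/197 − 1)/8 = 0.046 for the 0.25 row. Solving Step 3 for the stated LoA half-widths gives about 0.064 (0.4 row) and 0.113 (0.6 row).

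**Step 5: coverage, if the analysis used Table 3's formula.** Coverage of a nominal 95% interval for the mean difference is 2Φ(1.96 / √(1 + 8 × ICC)) − 1: about 90% / 86% / 78% / 71% at ICC 0.05 / 0.1 / 0.2 / 0.3.

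**Step 6: effect on the estimates.** The pooled variance has expectation SD² × (1 − 8 × ICC / 269). At ICC 0.3 that is 0.9% low in variance, or about 0.45% low in SD. The mean difference is unbiased.

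**The case against.** Several points on the other side are sound.

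- **The analysis intervals.** A reader might infer that the planned 95% intervals will be too narrow. The Statistical Analysis section does not establish this: it gives no variance formula, the article condenses a fuller protocol, and a separate analysis plan may specify a repeated-measures method. The coverage figures are therefore conditional. Such a plan could correct the analysis, but not the precision printed in Tables 3 and 4.
- **The footnoted rows.** A reader might infer that the design misses all its stated precision. Three of the four rows have slack. Both LoA rows hold at ICC 0.05, and the 0.6 row still just holds at 0.1.
- **The ICC.** It is assumed throughout. Each participant breathes at one rate from each of six categories, so rate-dependent error falls largely within participants and could keep the ICC low. This is why the table starts at 0.05.
- **The estimates.** A reader might infer that the reported agreement itself will be wrong. Bias and LoA are barely altered; what changes is the uncertainty around them. No acceptance limit is set in the article, so no stated decision is shown to flip.
- **The planning SDs.** The Background says of the earlier study that "few abnormal values were recorded in this investigation", while five of the six rate categories here lie outside 12 to 20. That is a separate matter from clustering. The article gives no SD by rate, so no size can be put on it, and the planned log transformation partly anticipates spread that grows with rate.

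**Conclusion.** The point holds for the stated precision. Tables 3 and 4 rest on independent observations, which is established by exact reproduction of all 29 rows, and their footnotes apply them to repeated epochs within 30 people. At an ICC of 0.1 to 0.3, the half-width of the mean rises from the stated 0.25 to 0.29–0.39, and from the stated 0.3 to 0.40–0.55. For the LoA it rises from 0.4 to 0.42–0.56, while the 0.6 row runs from 0.59 (still met) to 0.78. The 0.3 row fails at practically any positive correlation.

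The direction rests on positive within-participant correlation, which is plausible for one sensor placement in one session. The size rests on an ICC that the article does not give. Under-coverage of the planned intervals would follow only if they use Table 3's formula.

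**What to change.** 1. In Patient Population Size, replace the four footnoted precisions with values that take the 30 participants as the independent units, shown over a range of ICCs such as 0.05 to 0.3. Note that the planning SDs come from a study with few abnormal rates and add a larger SD; the half-widths scale in proportion, so an SD 25% larger (illustrative) widens each by 25%.
2. In Statistical Analysis, state that bias and LoA for each pair of methods will be estimated by repeated-measures Bland-Altman: a model of the difference with a random participant effect, LoA from the sum of between- and within-participant variance, and confidence intervals from the model or from a bootstrap that resamples participants.

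Recruitment stays at 30 and no further data are needed. Recruitment had not begun when the article was written. The cost is a wording change and somewhat less favourable stated precision.

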### Feasibility Assessment

The feasibility of performing this study with data collected from participants in a single session is based on upon previous successful observational studies that have been performed by the research team at PHT. These include the Using the Inflammacheck Device to Measure the Level of Exhaled Breath Condensate Hydrogen Peroxide in Patients With Asthma and Chronic Obstructive Pulmonary Disease (EXHALE) pilot study [13] and a previous study validating the RespiraSense device in patients with a large body mass index [14].

## Results

Recruitment to this study has not yet started as funding decisions are still pending. Therefore, results are not available at this stage. It is anticipated that the data required could be collected within 2 months of first recruitment to the study and data analysis completed within 6 months of the study start date.

## Discussion

### Rationale for Study Design

The Evaluation of Agreement of Breathing Rates Measured by a Novel Device, Manual Counting, and Other Techniques Used in Clinical Practice (VENTILATE) study will test the accuracy of the RespiraSense device at the extremes of RR. The selection of randomized RRs from within defined categories allows these abnormal RRs to be compared with normal RRs without introducing variability in the participant or the HCP. Additionally, video recording of the study procedures allows for independent sampling and monitoring of the ability of the HCP to manually count the RR by another HCP.

We chose to use healthy volunteers without underlying cardiopulmonary disease. It was not deemed safe or appropriate to use patients exhibiting extremes of RR in an observational study of this type. It was decided that the safest way to observe the RRs of interest for the study would be for healthy volunteers to consciously breathe at a given rate.

There are multiple points of contact during the screening visit to minimize the chance that participants fail to complete the study procedures. In addition to the standard practice of providing a PIS and allowing the participant time to consider what will be required of them during the study, the participants will also experience one of the higher RRs that they will be asked to perform during the study day. We chose to do this with the aim of reducing the number of participants who are unable to complete all of the study procedures.

Although the risk of harm to study participants is low, further measures will be taken to mitigate these risks. The potential risk of feeling unwell after breathing at high or low RRs will be mitigated by allowing participants to rest for longer than scheduled or to stop the procedure entirely should they feel unable to continue. A clinician will be present throughout the study procedures and will be able to stop the study at their discretion if they feel it is not safe or would be inappropriate to continue.

Additionally, the randomization of the RRs selected will be prescreened to prevent high variability between tachypnoea and bradypnea in a short space of time. A set of rates will be randomly generated by a custom random number generator which is programmed to select a rate from within each of the categories listed in the Study Design section. Each set generated will be reviewed by a clinician involved in the study and assessed for extreme variability and overall safety. Sets that pass this screening will be saved and assigned randomly to participants at the time of the study data collection. Examples of an acceptable and unacceptable set are shown in Table 5.

**Table 5 table5:** Acceptable and unacceptable respiratory rate sets.

	First rate	Second rate	Third rate	Fourth rate	Fifth rate	Sixth rate
Acceptable	6	10	23	17	28	32
Unacceptable	5	31^a^	22	14	26	9^a^

^a^Rates with extreme variability.

Another potential risk for participants using the RespiraSense device is the risk of reaction to the adhesive. This risk has two parts. The first is allergic reaction to the adhesive. This risk has been given a risk level of 2 by the PMD risk management team. A risk level of 2 indicates the risk has been reduced as low as possible. Although the severity of this potential risk is high, this occurrence has not been observed by PMD in any use of the device and has not been found in literature searches. This risk is mitigated by excluding volunteers who are allergic to medical-grade adhesive.

The second component is a mild reaction to the adhesive. This has been given a risk level of 2 by the PMD risk management team. A risk level of 2 indicates the risk has been reduced as low as possible. This risk is of low severity (mild reaction/discomfort) and moderate occurrence level. This risk is mitigated by excluding volunteers based on a skin fragility assessment. It is also possible that mild irritation that will not require medical intervention may be experienced for patients on oral steroids.

The procedures will be carried out in the simulation suite in the Learning and Development department which is located within the Resuscitation Department of PHT, and an experienced member of the resuscitation team will always be present. If a participant should become unwell as a result of the procedures, they will be withdrawn from the study and assessed by clinical team, and subsequently care will be escalated as appropriate.

The outputs of the RespiraSense sensor will not be used to assist any clinical decision, so there are no risks associated with use of the data collected with the device in this study.

### Limitations

The primary limitation to this study is the awareness from all participants that they are being monitored. This may alter the behavior of the participant and subsequently influence the data collected from them, known as the Hawthorne effect. The most likely influence that is expected to be seen is a change in the method of manual RR counting performed by the HCP. There is a large degree of variability in clinical practice when counting the RR. The awareness of being observed has the potential to encourage those who would use a method involving a shorter count and multiplication to employ a full count for 60 seconds. This will reduce the accuracy of the comparison between the RespiraSense device and current clinical practice.

### Conclusions

The VENTILATE study will provide further validation of the use of the RespiraSense device in subjects with abnormal respiratory rates. It will assess the device’s ability to measure abnormal RRs and compare with multiple other techniques used in various aspects of clinical practice. The results provided will help to guide the usefulness of the device in clinical practice in the future.

## Abbreviations

ECG: electrocardiogram
EXHALE: Using the Inflammacheck Device to Measure the Level of Exhaled Breath Condensate Hydrogen Peroxide in Patients With Asthma and Chronic Obstructive Pulmonary Disease pilot study
HCP: health care provider
LoA: limit of agreement
NEWS: National Early Warning Score
NICE: National Institute for Clinical Excellence
PHT: Portsmouth Hospitals NHS Trust
PIS: participant information sheets
RR: respiratory rate
VENTILATE: Evaluation of Agreement of Breathing Rates Measured by a Novel Device, Manual Counting, and Other Techniques Used in Clinical Practice
